### Inclusion criteria

Aged 18 years or greater.Receiving HD three times per week for ESKD, for at least 3 months.Having proven mental capacity to understand the study and give informed consent.

### Exclusion criteria

Established diagnosis of dementia in a memory clinic or specialised service.Receiving acetylcholinesterase inhibitors.Receiving antipsychotic or antidepressants unless stable on treatment for at least 6 weeks.Current participation in a study of an investigational medicinal product.Inter-current infection.An operation date for a living donor kidney transplant within the period of the trial.Patients expected to survive less than 1 year according to the treating nephrologist.Patients prone to intra-dialytic hypotension or cardiovascular instability during HD according to the treating nephrologist.Patients who are currently taking triptans, dopamine antagonists, tramadol, sedative and opioid analgesics.Patients who have a known diagnosis or have other psychiatric conditions, including severe depression, bipolar affective disorder, severe anxiety, panic disorder, substance misuse or psychosis.Currently involved in another intervention study.

### Inclusion criteria (carers)

Adult above the age of 18.Consents to take part in the study.Speaks English.

### Exclusion criteria (carers)

Not in regular contact with the patient.Any apparent personal or psychological conflicts with the patient that could skew their feedback as judged by the research team.Evidence for very poor physical health that would prevent them from completing the study.

### Participant withdrawal

Participants are free to withdraw at any time and this will not affect their future care. They will be asked if they wish to withdraw completely, and have all data removed from the study, or just from the point of withdrawal.

### Randomisation and concurrent treatments

Currently in the UK, temperatures between 35 °C and 37 °C are empirically used in dialysis; however, the best temperature is not known and may be differentially tolerated depending on the patients’ own core temperature [39]. International clinical guidelines recommend a minimum temperature for the dialysate of 35 °C mainly for cardiovascular stability [40, 41]. All consenting participants eligible for inclusion will be randomised on a 1:1 basis to the control group dialysate temperature of 36.5 °C for 12 months or cooled dialysate temperature of 35 °C for 12 months. Randomisation will be stratified by age group using a secure internet-based system that concealed treatment allocations (Sealed Envelope, London, UK). The randomisation software (https://www.sealedenvelope.com/simple-randomiser/v1/trials/e-checked) contains the randomisation sequence that is not available to the research personnel (unless blinding needs to be broken in case of SAEs). The software requires the details of the patients to be entered before the randomisation arm is revealed thereby maintaining concealment of the allocation. This process will be performed by a research nurse who will not be involved with any other part of the study.

### Study interventions

Patients will be randomised to one of two groups: the intervention and the control group. Both groups will have a pre-study run-in phase of 2 weeks to establish pre-dialysis temperature with a tympanic thermometer taken at each session. The control group will then use the standard dialysate temperature of 36.5 °C. The intervention group will start off using a dialysate temperature of 36 °C. Thereafter, the dialysate temperature will be reduced every 2 weeks by 0.5 °C until a temperature of 35 °C is reached. Patients who fail to tolerate the temperature of 35 °C, the lowest tolerated temperature, will be carried over to the end of the study. Tympanic and dialysate temperature will be recorded at every session regardless of study group to aid monitoring of protocol adherence and allow an interim analysis of patient’s temperatures to ensure a clear temperature separation of the study groups. The research nurse will assess temperature tolerability every 2 weeks using a Tolerability of Low Temperature Dialysis Questionnaire for the first 6 weeks. The patients will not be informed to their group allocation nor the temperature setting of the machine to enable unbiased comparison of the tolerability of the intervention. The investigators carrying out cognitive assessment and study related procedures will also be blinded to their group allocation. The clinical nursing staff must be unblinded to deliver the intervention, but any temperature display on the machine will be concealed from the patients. Any patient from the control group and intervention group complaining of feeling cold during haemodialysis session will be provided with an extra blanket to aid tolerance and improve comfort. But if patient could not tolerate the lower temperature to the point that they felt they could terminate the session, the temperature will be increased back to the previous setting. This ensures a minimum between-group temperature separation of 0.5 °C for the expectedly few intervention group patients who can only tolerate dialysate temperature reduction to 36 °C. In a previous similarly designed study, only 2 of 73 participants required this protocol deviation [28].

### Blinding

This study design allows double blinding of both patients and investigators. All outcomes are measured at 0 (baseline), 6 and 12 months by a blinded rater, on a non-dialysis day when the best performance is expected [16, 17]. Blinding of the rater could be compromised if the rater visited the patient during HD as machine settings might be visible. Testing patients shortly before a HD treatment might be inconvenient with implications for recruitment and retention. Therefore, in this study, all assessments are conducted in domiciliary visits in the homes of patients or a mutually agreed venue. The carer assessment will also be taken at months 0, 6 and 12 by a blinded independent rater. The only person for whom blinding will not be practical is the clinical nursing staff in the haemodialysis unit setting the temperature of the machine based on the patient’s allocation. However, these staff will have no contact regarding the temperature settings with either patients or investigators performing the assessments regarding the temperature settings.

### Assessment and data collection

#### Data collection

The data collection schedule is summarised in Table 1. Once a participant has given valid informed consent, there will be three study visits at baseline, 6 and 12 months. Data collected will include baseline demographics. The research team are committed to inclusion. Local audit data showed that after English, Urdu and Bengali are the two most used native languages. Whilst inclusion criteria include a good command of English language, we will ensure where possible assessments are available in Urdu and Bengali.

#### Qualitative data and quantitative data to inform future trial design

The main aim of the qualitative component is to assess issues related to patient recruitment. This will include practicalities of implementing cooler dialysate, adherence to treatment, effectiveness of blindness process and identification of factors that may affect routine practice of treatment in various centres. We will apply thematic analysis to qualitative data collected from semi-structured interviews.

#### Tolerability of low temperature

Patients are asked about their ability to tolerate the low temperature and their level of comfort. They are also asked whether they need any extra support. The questionnaire was locally designed and used in an unpublished pilot study where it showed face validity and reliability.

#### Confusion Assessment Method (CAM)

The Confusion Assessment method (CAM) is a valid tool that is brief to administer and excludes the effect of delirium on cognitive performance [33]. The CAM will be used to exclude delirium before each study visit and only if it indicates delirium would assessments be postponed by 2 weeks or as directed by the treating clinician.

#### Montreal Cognitive Assessment (MoCA)

The MoCA is a 30-point brief test of global cognitive function taking approximately 10 min to administer [31]. There are three alternate English language forms designed to minimise practice effects in longitudinal studies. The MoCA is included as the planned primary outcome in a future definitively powered clinical trial. A prior study validated the German language version of the MoCA in HD patients against a detailed neuropsychological battery of cognitive tests [42]. To our knowledge, this study will provide the first English language validation of the MoCA in HD patients against the Cogstate a detailed assessment of cognitive function. The MoCA is also available in Urdu and Bengali language, the two most common non-English native languages used by participants in the research sites.

#### Cogstate

The Cogstate system is a well validated computerised test that assesses a diverse range of key cognitive skills [32]. The Cogstate is available in 90 languages and uses multiple ‘parallel’ versions of the tests, thus minimising practice effects. The use of reliable repeated measures is of particular utility in studies in which participants may not be blind to their treatment status. The Cogstate system was also selected to reduce test fatigue and simplify test administration, whilst preserving strong test-retest reliability (rho = 0.81–0.89). It has the advantages of being portable, short (20–30 min), game-like in presentation and thus motivating, cross-culturally adaptable and language independent.

#### Quality of life

We will use the Assessment of Quality of Life (AQoL-6D) scale to measure patient’s quality of life [34]. This is a generic health-related quality of life instrument, which provides a profile relative to four life dimensions. Administration typically takes 5 to 10 min.

#### Activities of daily living

The Bristol Activity of Daily Living Scale will be used to measure activities of daily living in relation to cognitive impairment [35]. This is an informant-rated interview of 20 items each rated on 60-point scale. It was designed for use in patients with cognitive impairment.

#### Anxiety and depressive symptoms

The Hospital Anxiety and Depression Scale is a valid measure of anxiety and depression in patients with frequent hospital admissions where higher scores reflect greater depression and anxiety [37]. Systematic review identified a threshold score of 8 out of 21 for anxiety or depression [43] and 15 out of 21 as appropriate to refer patients into mental health care pathways.

#### Carer burden assessment

We will measure carer burden using Caregiver Burden scale, which was developed to assess perceived burden among caregivers of family members with cognitive impairment [36].

### Physiological measurements

#### Intradialytic hypotension

Intradialytic hypotension is an important secondary outcome for this trial as reducing these episodes are a plausible mechanism by which dialysate cooling might prevent cognitive decline. Intradialytic hypotension has been defined in several ways in prior studies making comparisons challenging. Symptoms are also infrequently self-reported by patients making symptom-based definitions problematic [44]. Recent data demonstrates that brain ischemia can occur at a variety of thresholds that would not typically be recognised as intradialytic hypotension [45]. A recent 77 patient study reported systolic blood pressure (BP) less than 100 mmHg or a 20% reduction in systolic BP from baseline as thresholds that maximised the probability of a nursing intervention rather than a session remaining asymptomatic [44]. Authors of a study of 11,801 HD patients reported that intradialytic hypotension defined as systolic BP less than 90 mmHg was potently associated with greater mortality [12] whilst definitions based on patient symptoms, nursing interventions or relative decreases in BP during dialysis were not. For this study, BP will be recorded as in routine clinical practice, before start and after end of dialysis session. In addition, BP will be checked every 30 min during HD treatment. For analysis, intradialytic hypotension will be defined as a fall in systolic BP during dialysis greater than 20% from baseline or absolute systolic BP less than 90 mmHg. Nursing interventions for intradialytic hypotension (slowing down ultrafiltration, giving additional fluid) are routinely recorded.

#### Intradialytic weight gain, ultrafiltration volume and ultrafiltration rate

Weight gain between dialysis sessions, the volume of fluid removed per treatment session (ultrafiltration volume) and the rate at which it is removed (ultrafiltration rate) will be extracted from routinely recorded HD treatment records and transferred monthly into the case report form by research staff after verification for any missing or implausible values. The feasibility of this process will be reported.

#### HD recovery time

The HD recovery time will be recorded by a simple question, “How long does it take you to recover from a dialysis session”. A mean of 3 reported recovery times across a dialysis week (Monday, Wednesday and Friday or Tuesday, Thursday and Saturday) will be assessed at baseline, 6 months and 12 months. Longer self-reported recovery time is independently associated with reduced health-related quality of life, increased hospitalisation and reduced survivals [38].

#### Adherence to treatment allocation

Adherence to the allocated dialysate temperature will be regularly checked and recorded by research staff at each research site using electronic records which enable distinction between prescribed and delivered dialysate temperature. Analysis would be by intention to treat.

### Outcome measures

#### Primary outcome measure

The primary outcome measure is change in cognition from baseline to 12 months, assessed by Montreal Cognitive Assessment (MoCA, v7.2) [31], in the standard and low temperature dialysis groups.

#### Secondary outcome measures

Frequency of intradialytic hypotension: to measure the frequency of intradialytic hypotension as an explanatory outcomeRecruitment rates: to measure recruitment to inform the design of a larger clinical trialAttrition rates: to measure attrition rates to inform the design of a larger clinical trialNon-recruitment reasons: to record reasons for non-recruitment and study attrition to inform the design of a larger clinical trial.Depression rates: to measure depressive symptoms in the targeted population using the Hospital Anxiety and Depression Scale (HADS) [37].Detailed assessment of cognition: to assess the acceptability and usability of a computerised cognitive assessment method (Cogstate) [32] for measuring cognition in dialysis patients, especially those from ethnic minorities. The Cogstate battery contains measures attention, psychomotor function, executive function and memory. The main outcome for this set of tests will be a composite cognitive scoreTo assess the burden of study-related interventions and assessments on carers using the Bristol Activities of Daily living scale and Carers Burden Assessment [36].To assess the administration and suitability of the chosen method for measuring carers’ burden in this group.To assess quality of life and activities of daily living in participants using the Assessment of Quality of Life (AQoL-6D) questionnaire [34].

### Data analysis

Data analysis will be performed by statisticians who are blinded to participant treatment allocation. A mixed method approach will be used, utilising semi-structured interviews, questionnaires and measurement of cognitive function. The 12 month follow-up period will be the key assessment time for all outcomes. Normally distributed data will be presented as mean (SD), skewed data as median (IQR) and categorical data as number (percent). The main aim of the qualitative component is to assess issues related to patient recruitment. This will include practicalities of implementing cooler dialysate, adherence to treatment, effectiveness of blindness process and identification of factors that may affect routine practice of treatment in various centres. We will apply thematic analysis to qualitative data collected from semi-structured interviews. Interviews will be on a 1:1 basis and will be audio-recorded. They will be transcribed by the research assistant and will be anonymised and securely stored, accessible only by the research team. The purpose of the quantitative analysis is to estimate the mean and standard deviation for MoCA at baseline and follow-up in both trial arms and obtain an estimate of the attrition. For all analysis, the level of significance will be set at 5%, so that 95% confidence intervals will be presented. This is a feasibility study and statistically or clinically significant changes in outcomes between groups are unlikely; hence, no between-group inferential comparisons will be made. However, a preliminary estimate of a treatment effect is relevant to sample size estimation of future definitive trials. As an exploratory analysis, we will conduct a complete case analysis of the primary and secondary outcomes. A linear regression model will be used for continuous outcomes (e.g. MoCA) and a logistic regression model will be used for binary outcomes. Each model will include the baseline measurement and treatment arm as independent variables. All patients randomised to their respective study arms will be included in the intention to treat analysis. Missing data, if any, will be managed using the last-observation carried forward approach. There will be no interim analysis of the data, though the safety data resulting from any SAE will be collated and made available to the Trial Steering Committee. All analysis will be conducted in Stata 15.

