### Primary objective

The primary objective is to test the feasibility of the investigation of lower temperatures of dialysis fluid in preventing the decline in cognitive function and improve the quality of life in HD patients.

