### Study setting and population

Patients will be recruited through the renal clinics at four HD units in the United Kingdom at Birmingham Heartlands Hospital, Runcorn Road Renal Unit, Solihull Hospital and Castle Vale Renal Unit. All these HD units are under the collective organisation of the University Hospitals Birmingham NHS Foundation Trust. The study aims to recruit 90 patients allocating 45 patients in the intervention and 45 patients in the control group. Suitable patients will be identified by the direct care team. The care team will speak with the suitable patients to see if they are happy to have their details passed on to the research team for further discussion. If the patient agrees, the research team will contact the patient and determine eligibility. Suitable patients will be identified through searching records in the four participating units. An information pack will be given to the patient (see Additional file 1), who will be given 24 h to read the information and ask any questions they may have. The research team will then contact the patient, in a pre-agreed manner (i.e. next clinic visit, via telephone) to see if they have any further questions or would like to participate in the study. If they would like to participate in the study they will arrange to meet and complete the consent form (see Additional file 2).

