### Sample size

The outcome data from this feasibility study will be used to inform the sample size calculation for the definitive trial, by providing estimates of the primary outcome and its variability and the expected attrition. The study aims to recruit a total of 90 patients from four sites. Lancaster and co-workers outlined the key aspects of feasibility studies and indicated at least 30 patients per each arm are required to identify the sample variability (standard deviation) in key variables to enable the calculation of power for testing hypotheses in subsequent definitive studies [46]. The primary outcome in the definitive study is likely to be a value from the MoCA. With 45 patients in each arm, and if the mean (SD) value of the MoCA is 27 (2) in the control and intervention arms at the study start, we could expect a 95% confidence interval to range from 26.4 to 27.6 in each arm. This will give adequate precision for the estimate required in the study. With 45 patients in the control arm, and assuming a mean (SD) value of MoCA of 22 (3) after 12 months, we could expect a 95% confidence interval to range from 21.1 to 22.9. In the intervention arm, assuming a mean (SD) MoCA value of 25 (3) after 12 months, we could expect a 95% confidence interval to range from 24.1 to 25.9. Furthermore, with a total sample size of 90 patients, with an expected loss of 20% of the patients, a 95% confidence interval could be produced, ranging from 70.2 to 87.7%.

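### The stated reason for making no between-group inference does not fit the plan's own assumed MoCA values, the estimated treatment effect is allowed to inform the definitive sample size, and the primary outcome does not match the feasibility objective

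*Protocol article*

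**What the plan says.** **Inference.** After describing the study as a feasibility study, the Data analysis section states that "statistically or clinically significant changes in outcomes between groups are unlikely; hence, no between-group inferential comparisons will be made". Shortly before, it says: "For all analysis, the level of significance will be set at 5%, so that 95% confidence intervals will be presented". It goes on to plan, as exploratory complete-case analyses, linear and logistic regressions with baseline value and treatment arm as covariates.

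**Use of the effect estimate.** The same section adds that "a preliminary estimate of a treatment effect is relevant to sample size estimation of future definitive trials". The Sample size section says that outcome data from this study will inform the definitive calculation through estimates of the primary outcome, its variability and attrition.

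**Assumed values.** The Sample size section takes a baseline MoCA of 27 (SD 2) in both arms and 22 (SD 3) in the control arm at 12 months. It continues: "In the intervention arm, assuming a mean (SD) MoCA value of 25 (3) after 12 months". It expects 20% loss. The recruitment target is given under Study setting and population: "The study aims to recruit 90 patients allocating 45 patients in the intervention and 45 patients in the control group".

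**Objective and outcomes.** "The primary objective is to test the feasibility of the investigation of lower temperatures of dialysis fluid", according to the Primary objective section. The Secondary objectives section sets the conditions for going ahead unmodified: recruitment of at least 50% of eligible patients, attrition below 20% by 6 months and compliance of 60%. Yet "The primary outcome measure is change in cognition from baseline to 12 months", measured by MoCA. Recruitment and attrition appear as secondary outcomes, and compliance is not in the outcome list.

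**The concern.** Three things do not sit together.

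- Improbability of a significant difference is offered, alongside the feasibility label, as the reason for not comparing the arms. The only numbers that the protocol gives for the two arms at 12 months describe a difference that would almost certainly be significant.
- Having set comparison aside, the plan gives the estimated effect a role in sizing the next trial. The cited rationale for the sample size (at least 30 per arm) concerns estimating a standard deviation, not a difference between arms. A chance large estimate would lead to a definitive trial that is too small, and a chance small one to a trial that is needlessly large or never run.
- The objective and the progression rule are about feasibility, but the single primary outcome is a cognitive score. The measures that decide progression are secondary or, for compliance, unlisted.

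The main product of this trial is the design of the next one, so these are the statements that most need to be right.

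**Working it through.** **1. The plan's own figures reproduce.** Interval for a mean: mean ± t(0.975, 44) × SD/√45, with t = 2.015.
- Baseline: 2.015 × 2/√45 = 0.60, giving 26.4 to 27.6.
- Control at 12 months: 2.015 × 3/√45 = 0.90, giving 21.1 to 22.9.
- Intervention at 12 months: the same half-width, giving 24.1 to 25.9.
- Retention of 72/90, exact binomial: 70.2% to 87.7%.

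All agree with the Sample size section. The two 12-month intervals do not overlap.

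**2. Power implied by the assumed values.** Difference 25 − 22 = 3 points; SD 3; two-sided 5% (sidedness is not stated and is taken from the 95% intervals). The noncentrality is 3/(3√(2/n)).
- n = 45 per arm: 4.74, power 99.7%.
- n = 36 per arm (45 less 20%): 4.24, power 98.7%.

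The protocol states no power; these figures are derived from its inputs. If change scores are analysed instead, with baseline SD 2, follow-up SD 3 and an assumed correlation between 0 and 0.8, power at 36 per arm runs from 93.6% to about 100%.

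**3. Precision of the estimated difference, 36 per arm.** The exploratory analysis is complete-case, so 36 per arm is the relevant number.
- Unadjusted: SE = 3 × √(2/36) = 0.707; half-width = 1.994 × 0.707 = 1.41 points.
- Adjusted for baseline, as the regression specifies. The correlation is not given; 0.6 is assumed. Residual SD = 3 × √(1 − 0.36) = 2.4; SE = 2.4 × √(2/36) = 0.566; half-width = 1.995 × 0.566 = 1.13 points.

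**4. What that noise does to a sample size.** Per-arm size for 90% power at two-sided 5% is 2 × (SD × (1.960 + 1.282)/d)², which is about 189.1/d² at SD 3 and 121.0/d² at SD 2.4. A true difference of 1 point is assumed. The middle half of estimates is 1 ± 0.6745 × SE.

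| | Unadjusted (SD 3) | Correlation 0.6 (SD 2.4) |
|---|---|---|
| Middle half of estimates | 0.523 to 1.477 | 0.618 to 1.382 |
| Implied size per arm | 691 down to 87 | 317 down to 63 |
| Size needed at d = 1 | 189 | 121 |
| Ratio of the two ends | about 8 | about 5 |

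Half of all such trials would give an estimate outside these ranges.

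**5. Objective, progression rule and outcomes side by side.**

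| Progression measure (Secondary objectives) | Place in the outcome list |
|---|---|
| Recruitment | Secondary |
| Attrition | Secondary |
| Compliance | Not listed |

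The section on adherence to treatment allocation already provides for recording delivered dialysate temperature, so data for an adherence measure exist.

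**The case against.** **The 22 and 25 are not a planned effect.** A reader might infer that the trial is designed to detect 3 points with 99% power. The text does not support that. The section is a precision argument with no power, target difference or test, and the interval widths depend only on SD and n. This stands. What remains is that the values are not called illustrative, that different means were not needed to show a half-width of 0.9, and that they jar with the reason given for not comparing.

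**The 5% sentence does not authorise testing.** A reader might infer a contradiction between a significance level and a bar on inference. The sentence ties the 5% to presenting 95% intervals, and the regressions are called exploratory. No p-value is mentioned. This also largely stands, and a short clarification is enough.

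**The plan does not commit to using the observed effect as the target.** It says that the estimate is relevant and that outcome data will inform the calculation. It does not exclude a minimum important difference. That is so, but it names no such difference either, and the wording leaves the way open.

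**The sample-size ranges rest on assumptions.** The 1-point effect is not in the protocol, and the unadjusted SD ignores the planned baseline adjustment. Adjusting at a correlation of 0.6 narrows the spread from about eight-fold to about five-fold. The instability remains.

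**The progression criteria are already prespecified.** They are, so the decision is not hidden. The mismatch lies in how outcomes are labelled, and in compliance having no place among them.

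**Conclusion.** The concern holds in this limited form and should be fixed. Declining to test between arms is legitimate in a feasibility trial; the fault is in the reason given. The protocol's own assumed values imply about 99% power for a 3-point difference, so it cannot also rest the decision on such a difference being improbable without marking those values as illustrative.

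The more consequential part is the role left open for the estimated effect. Its 95% half-width of about 1.4 points unadjusted depends only on the protocol's SD, sample size and expected loss. The figure of about 1.1 depends also on an assumed correlation of 0.6, and the five- to eight-fold spread in implied sample size on an assumed true difference of 1 point. Other assumptions would move the numbers, but an estimate this imprecise is not a sound basis for a target difference.

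The primary outcome does not match the primary objective or the progression rule. This is a labelling fault with no effect on what is collected.

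**What to change.** 1. Justify the absence of between-group testing by the feasibility aim, and delete the argument from improbability.
2. Label the 12-month values of 22 and 25 as illustrating per-arm precision only.
3. State that the definitive trial's target difference will be a pre-agreed minimum important MoCA difference, and that this trial supplies only the SD, the baseline to 12-month correlation, attrition and adherence.
4. State that treatment coefficients are exploratory and are reported with 95% confidence intervals only.
5. Make the progression measures (recruitment, attrition and compliance with the allocated temperature) the primary outcomes, and list MoCA change as the candidate outcome for the definitive trial.

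The cost is rewording of the outcome, analysis and sample size sections and a registry update for the outcome order. Data collection does not change.

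### Randomisation is stratified by age group but the regression models leave age group out, so the exploratory linear models will report slightly over-wide confidence intervals (minor)

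*Protocol article*

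**What the plan says.** The section Randomisation and concurrent treatments says that eligible, consenting participants "will be randomised on a 1:1 basis", and adds: "Randomisation will be stratified by age group using a secure internet-based system that concealed treatment allocations". No other factor is named, and neither the age cut-points nor the number of age groups is given.

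The Data analysis section sets out the models: "A linear regression model will be used for continuous outcomes (e.g. MoCA) and a logistic regression model will be used for binary outcomes". It then fixes their content: "Each model will include the baseline measurement and treatment arm as independent variables". Age group is not added to any model elsewhere in the article.

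The same section limits the role of these models. They come under this sentence: "As an exploratory analysis, we will conduct a complete case analysis of the primary and secondary outcomes". Because significant differences are thought unlikely, the authors write "hence, no between-group inferential comparisons will be made". They nevertheless set a 5% level with 95% confidence intervals for all analyses, and note that "a preliminary estimate of a treatment effect is relevant to sample size estimation of future definitive trials". The quantity to be estimated is given separately: "The purpose of the quantitative analysis is to estimate the mean and standard deviation for MoCA at baseline and follow-up in both trial arms".

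**The concern.** Stratified allocation forces the arms to be close to balanced on age group. If age group predicts the outcome beyond the baseline score, the treatment estimate then varies less from one possible allocation to another than it would under simple randomisation. An ordinary regression without age group does not take this into account. It leaves the age-related variation in the error term and reports a standard error as if the arms could have differed by chance on age.

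What is at stake is the width of the interval around the exploratory treatment estimate. The article describes that estimate as relevant to sizing a later trial. This is not a detail left to a separate analysis plan, because the article states the covariate list for every model and the list omits the one factor used to randomise.

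**Working it through.** **Inputs.** From the protocol article: 90 patients, 45 per arm, 1:1 allocation stratified by age group; models with baseline and arm only; 20% expected loss; MoCA mean (SD) 27 (2) at baseline, and 22 (3) and 25 (3) at 12 months in the control and intervention arms. Not in the documents, so assumed: R², the share of the 12-month variance left after baseline that age group explains, taken over 0 to 0.20.

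**The plan's own figures.** The Sample size section gives confidence intervals for single-arm means, mean ± t(0.975, 44) × SD/√45 with t = 2.015:

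- Baseline: 27 ± 2.015 × 2/6.708 = 27 ± 0.60, that is 26.4 to 27.6.
- Control, 12 months: 22 ± 2.015 × 3/6.708 = 22 ± 0.90, that is 21.1 to 22.9.
- Intervention, 12 months: 25 ± 0.90, that is 24.1 to 25.9.
- Retention of 72/90, exact (Clopper-Pearson) interval: 70.2% to 87.7%.

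All four reproduce. The three MoCA intervals use raw per-arm SDs, so no model covariate enters them.

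**Effect of omitting age group in a linear model.** Let σ be the residual SD after baseline and n the number per arm.

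- Reported SE without age group ≈ σ√(2/n).
- True SE under stratified allocation ≈ σ√(1 − R²) × √(2/n).
- Ratio = 1/√(1 − R²).

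This gives 1.000 at R² = 0; 1/√0.98 = 1.010; 1/√0.95 = 1.026; 1/√0.90 = 1.054; 1/√0.80 = 1.118.

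**Simulation check.** 90 patients, two age groups of equal probability, blocks of 4 within age group, baseline slope 0.6, no treatment effect, 4,000 runs per row. The number of strata and the block size are assumptions.

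| R² | Model SE, no age | Empirical SE, no age | Type I error, no age | Model SE, with age | Empirical SE, with age | Type I error, with age | Ratio of model SEs |
|---|---|---|---|---|---|---|---|
| 0 | 0.2107 | 0.2106 | 4.8% | 0.2107 | 0.2106 | 4.8% | 1.000 |
| 0.02 | 0.2112 | 0.2096 | 4.8% | 0.2091 | 0.2096 | 5.1% | 1.010 |
| 0.05 | 0.2114 | 0.2100 | 4.9% | 0.2059 | 0.2099 | 5.4% | 1.027 |
| 0.10 | 0.2118 | 0.1975 | 3.8% | 0.2010 | 0.1970 | 4.6% | 1.054 |
| 0.20 | 0.2116 | 0.1890 | 3.1% | 0.1891 | 0.1882 | 4.7% | 1.119 |

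The ratio of model SEs (0.2118/0.2010 = 1.054, for example) follows the formula. Without age group the model SE clearly exceeds the empirical SE at R² of 0.10 and 0.20. At 0.05 or below that gap is within simulation error. The two models' estimates have almost the same empirical SE, so the fault lies in the reported SE and not in the estimate.

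**In MoCA points (illustration).** Take 36 complete cases per arm after 20% loss and a residual SD of 3, which is generous because it is the raw 12-month SD with nothing removed for baseline. The half-width is 1.96 × 3 × √(2/36) = 1.39 without age group. With it, the half-width is 1.39 × √0.95 = 1.35 at R² = 0.05 and 1.39 × √0.90 = 1.31 at R² = 0.10.

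**Logistic models.** The ratio above is a linear-model result. In logistic regression, adding a prognostic covariate generally enlarges the SE of the log odds ratio and changes the odds ratio being estimated to one conditional on that covariate.

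**The case against.** The strongest reply is that nothing in this trial depends on the affected interval. The models are exploratory and no between-group inference is planned. The criteria for carrying the protocol forward, listed under Secondary objectives, are recruitment of at least 50%, attrition below 20% by 6 months and compliance of 60%; none uses a regression. The error is also conservative, baseline MoCA may already absorb part of any age effect, and R² is not known. For scale, with 36 per arm the 95% interval for a per-arm SD runs from about 19% below to 30% above its estimate (√(35/53.2) = 0.81; √(35/20.6) = 1.30). All of this stands, and it limits the severity. It does not remove the mismatch between how patients are allocated and how the models are written.

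A reader might go further and infer that an overstated residual SD is passed to the definitive trial, inflating its sample size by 1/(1 − R²), or about 5% to 11% at R² of 0.05 to 0.10. The documents do not support that. The Data analysis section sets out to estimate raw per-arm means and SDs, the Sample size section works with raw SDs, and no residual SD is named. Covariates do not change a raw SD. The inference would need two further steps that the article does not take: choosing a model residual SD to size the later trial, and adjusting for age group in that trial as well. The primary outcome is a change score, so someone might later reach for a residual SD, but that remains conditional.

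The article also gives no reason for choosing age as the stratification factor, so a strong link with cognition should not be taken as stated.

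**Conclusion.** The mismatch is real and its effect is small. Randomisation uses age group and every specified model omits it. In the linear models the treatment estimate is unbiased, but its model-based SE and 95% confidence interval are too wide by about 2.6% to 5.4% if R² is 0.05 to 0.10, and not at all if R² is 0. These figures rest wholly on the assumed R² and on near-balance of age group between the arms. They do not carry over to the logistic models. Nor does the omission make intervals too narrow or raise the false-positive rate; where it has an effect, that effect is in the opposite direction. Severity is minor.

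**What to change.** In the Data analysis section, replace the covariate sentence with, for example: *Every regression will adjust for the baseline value of the outcome, the allocated arm and the age group used at randomisation.* Add that odds ratios from the logistic models are then conditional on age group, and that no gain in their precision is expected.

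If the team later sizes a definitive trial from a model residual SD, and that trial will also adjust for age group, the SD should come from the model that includes age group. Reporting it both with and without age group would make the choice visible.

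The cost is slight. Age group is already held for randomisation, so no new data are needed. It adds one model term if there are two age groups and more if there are several; the article does not give the number, so it should be checked before the term is added to logistic models with at most 90 patients.
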